### Endpoints

#### Primary endpoints

The primary endpoint is the percent change in areal BMD of total hip and lumbar spine as measured by dual-energy x-ray absorptiometry (DXA) (Hologic Discovery, Waltham, MA, USA) from baseline until 12 months (Table 2).

**Table 2 Tab2:** Primary and secondary endpoints

	Measurement	Site	Time (months)
Primary endpoints			
Δ Bone mineral density	DXA	Total hip Spinal region	12
Secondary endpoints			
Δ Bone mineral density	DXA	Total hip Spinal region	6, 18, and 24
Δ Bone microarchitecture	HR-pQCT	Distal radius Distal tibia	6, 12, 18, and 24
Δ Bone biomarkers	P1NP CTX, sclerostin	Serum	3, 6, 12, 18, and 24
Δ Physical biomarkers	TUG SPPB		3, 6, 12, 18, and 24
	Dynamometer	Hand grip	
	Nottingham power rig	Leg extensor	
Δ Quality of life	EQ-5D		12 and 24
Δ Fear of falling	FES-I		12 and 24
Physical activity	IPAQ		0, 12, and 24
Adherence to WBV	Training logbook		Continuously
Falls	Falls calendar		Continuously

*Δ* change from baseline; Time is measured in months; *DXA* dual-energy x-ray absorptiometry; *HR-pQCT* high-resolution peripheral quantitative computed tomography; *P1NP* procollagen type-1 amino-terminal propeptide; *CTX* carboxy-terminal type-1 collagen crosslinks; *TUG* Timed Up and Go; *SPPB* Short Physical Performance Battery; *FES-I* Falls Efficacy Scale International; *IPAQ* The International Physical Activity Questionnaire; *EQ-5D* EuroQoL 5-dimension, 5-level questionnaire, *WBV* whole-body vibration

BMD is chosen as an endpoint since it is an important determinant of fracture risk and is used to diagnose and assess response to treatment in osteoporotic patients [1, 21].

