**Methods/design:**

PaVOS is a multicenter, assessor-blinded, superiority, two-armed randomized controlled trial (RCT).

Postmenopausal women (*n* = 40, aged 50 years and older) starting taking PTH 1-34 from outpatient clinics will be randomized and assigned to a PTH 1-34 + WBV-exercise group (intervention group), or a PTH 1-34-alone group (control group).

The intervention group will undergo WBV three sessions a week (12 min each, including 1:1 ratio of exercise: rest, 30 Hz, 1 mm amplitude) for a 12-month intervention period. Both the intervention and the control group will receive PTH 1-34 treatment (20 μg s.c. daily) for 24 months. After 12 months the WBV group will be re-randomized to stop or continue WBV for an additional 12 months.

The primary endpoint, bone mineral density (BMD), will be measured by dual-energy x-ray absorptiometry of the total hip and the lumbar spine.

Secondary endpoints, bone microarchitecture and estimated bone strength, will be assessed using high-resolution peripheral quantitative computed tomography (HR-pQCT) of the radius and tibia. Serum bone turnover markers (carboxy-terminal collagen crosslinks (CTX), amino-terminal propeptide of type-I collagen (P1NP), and sclerostin) and functional biomarkers (Timed Up and Go (TUG), Short Physical Performance Battery (SPPB), grip strength, and leg extension power) will be measured to assess the effect on bone turnover, muscle strength, balance, and functionality. Quality of life (EQ-5D), physical activity (IPAQ) and fear of falling (FES-I) will be assessed by questionnaires. Data on adherence and falls incidence will be collected.

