### Statistical analysis

#### Sample size determination

The inclusion of 32 participants (16 in each group) would give the study 80% power to detect a clinically significant additional increase of 22% in BMD with WBV (assuming a 9% increase of BMD in the PTH 1-34-alone group and 11% increase in the combined PTH 1-34 + WBV group, and assuming a standard deviation (SD) of the BMD increase of 2% [12]. Inclusion of 40 participants (20 in each group) will allow for a 20% dropout rate.

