#### Statistical methods and data managing

The intervention arm (PTH + WBV) is compared against the control arm for all primary analyses. We will use analysis of covariance (ANCOVA) and “percentage change” for primary outcome adjusting for baseline measurements. For secondary outcomes we will use a chi-squared test for binary outcomes, analysis of variance (ANOVA) and the *T* test for continuous outcomes, and for non-normally distributed continuous outcomes we will use log transformation or Wilcoxon’s match-pairs signed-rank test and the Kruskal-Wallis test.

All *p* values will be reported to four decimal places with *p* values < 0.001 reported as *p* < 0.001. STATA version 14 will be used to conduct analyses. For all tests, we will use two-sided *p* values with an alpha ≤ 0.05 level of significance.

The analyses will be conducted with the intention-to-treat method, and in order to investigate the effect of adherence and withdrawal a per-protocol analysis will be conducted. Missing data will be handled using multiple imputation. Study data is collected and managed using REDCap (Version 6.5.10 – © 2015 Vanderbilt University) electronic data capture tools hosted at the University of Southern Denmark [44]. Sequential study numbers will be allocated to study patients and entered into the recruitment log at the secure web database REDCap.

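### Two primary BMD sites are each tested at two-sided 0.05 with no rule for which result makes the trial positive, and the sample size covers one unnamed site

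*Protocol article*

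**What the plan says.** The section on primary endpoints reads "The primary endpoint is the percent change in areal BMD of total hip and lumbar spine". The sentence is in the singular, but its heading and Table 2 use the plural, and the primary row of Table 2 lists "Total hip Spinal region". The abstract also gives both sites: BMD "will be measured by dual-energy x-ray absorptiometry of the total hip and the lumbar spine". No composite, order or joint requirement is defined in any of these places.

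In the statistical methods section, the combined arm "is compared against the control arm for all primary analyses", using ANCOVA on percentage change with adjustment for baseline. The error rule is general: "For all tests, we will use two-sided" p values, "with an alpha ≤ 0.05 level of significance".

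The sample size section says that 32 participants, 16 per group, "would give the study 80% power to detect a clinically significant additional increase of 22% in BMD with WBV". It assumes increases of 9% and 11% and an SD of 2%. It does not say whether these figures describe the hip or the spine.

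**The concern.** A superiority trial needs one defined event that counts as a positive primary result. Here at least three rules fit the text: either site, both sites, or one site that the planning figures were meant for. They have different error rates and different power. Suppose that one site gives p below 0.05 and the other does not. With about 16 evaluable women per arm, such a split is a realistic outcome. The article would then allow it to be reported as success or as failure, and the choice could be made after seeing the data.

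The sample size does not settle the matter, because it treats BMD as a single unnamed quantity tested at 0.05.

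**Working it through.** **Inputs from the article.** Difference 11 − 9 = 2 percentage points; SD 2; 16 evaluable per arm; two-sided alpha 0.05; power 80%; dropout 20%; two primary sites.

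**Assumption not in the article.** The correlation between the hip and spine test statistics. It is varied from 0 to 1.

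**1. Reproduce the stated sample size (one comparison).**
- n per arm = 2(z₀.₉₇₅ + z₀.₈₀)² × SD²/difference² = 2 × (1.960 + 0.842)² × 4/4 = 15.7, so 16.
- Standardised effect at 16 per arm = 2 / (2 × √(2/16)) = 2.828. Power = Φ(2.828 − 1.960) = 80.7%.
- With dropout: 32 / 0.8 = 40.

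The stated figures reproduce for a single endpoint on the normal approximation. An exact t-test gives 78.1% at 16 per arm and needs 17, a minor difference.

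**2. Error if either site counts (no true effect at either).**
- Independent sites: 1 − 0.95² = 9.75%.
- Upper bound for any dependence: 0.05 + 0.05 = 10%.
- Otherwise: one minus the bivariate normal probability that both statistics lie within ±1.96.

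**3. Error and power if both sites are required.** With no effect at either site, the error is the probability that both statistics lie outside ±1.96. It can never exceed 5%, because each test alone is at 5%. Power is the bivariate normal probability that both statistics exceed 1.96 when each has mean 2.828. This assumes that both sites have the planned effect and SD.

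| Correlation | Either site: type I error | Both sites: type I error (both nulls true) | Both sites: power, 16 per arm |
|---|---|---|---|
| 0 | 9.75% | 0.25% | 65.2% |
| 0.5 | 9.1% | 0.9% | 69.7% |
| 0.7 | 8.35% | 1.65% | 72.2% |
| 0.8 | 7.8% | 2.2% | 73.8% |
| 0.9 | 7.0% | 3.0% | 75.9% |
| 1 | 5% | 5% | 80.7% |

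These rates count significance in either direction. Counting only results that favour vibration, the either-site rate is about 4.9% at correlation 0 and 3.9% at 0.8, against a nominal 2.5%.

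**4. Cost of testing at 0.025, the first step of Holm.** At 16 per arm, power for one site is Φ(2.828 − 2.241) = 72.1%, or 68.0% by exact t-test.

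**The case against.** Three points can be made in defence of the plan.

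First, the endpoint sentence is singular and joins the sites with *and*. That is compatible with requiring both, which needs no adjustment of alpha. This stands as a possible reading. It is not established, because the heading, Table 2 and the reference to all primary analyses are plural. It would also bring a power loss that the sample size section does not recognise.

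Second, the article does not say in so many words that each site gets its own ANCOVA. That is true. However, each site has its own baseline and no composite is defined, so one model per site is the natural reading.

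Third, this is a condensed article, and multiplicity procedures are often left to the SAP, which is not shown and may contain a rule. Silence alone would not be a finding. But the article is not silent: it sets 0.05 for all tests and applies this to two sites that it calls primary. What counts as a positive trial is also part of the primary hypothesis, not a programming detail.

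A reader might go further and infer that the trial's false positive rate is 8% to 10% instead of 5%. The article does not support that as a fact. The figure needs an either-site rule, which is not stated, and a correlation of no more than about 0.75, which is not given.

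**Conclusion.** The concern holds as a missing decision rule combined with a stated testing rule that does not control error under every reading. If either site suffices, the family-wise type I error is between 5% and about 10%. It approaches 5% only if the two sites are almost perfectly correlated. If both are required, the error is at most 5%, and power is about 65% to 81%; at correlation 0.99 it is still 79.2%, just under the stated 80%. If one named site decides, the stated error and power are correct, but the article does not name it.

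An inflated error rate is therefore a conditional result, not a demonstrated property of the trial. The power range assumes a 2-point gain and an SD of 2 at both sites, and all error and power figures use the normal approximation unless marked otherwise. The sample size of 32, or 40 with dropout, is not itself in error for a single endpoint.

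**What to change.** Before the 12-month data are compared by arm, state a fixed-sequence test:
- The sponsor names the site that the 9% versus 11% planning figures describe. The article does not identify it, so only the sponsor can.
- That site is tested first at two-sided 0.05.
- The other site is tested at two-sided 0.05 only if the first is significant.

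This holds the family-wise error at 5%, keeps the first test at the level used for the sample size and needs no more participants. It takes one or two sentences. The downside is that a significant result at the second site supports no confirmatory claim if the first site fails.

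Two alternatives are valid but cost more:
- **Both sites required.** Each stays at 0.05, but power must be restated, at about 65% to 81% for 16 per arm depending on the correlation.
- **Holm across the two sites.** No order is needed, but the first step is at 0.025, where power for a single site at 16 per arm is about 68% to 72%.

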#### Secondary endpoints

##### Bone mass

Change in areal BMD of total hip and lumbar spine is measured by DXA from baseline until 6, 18, and 24 months (Table 2).

##### Bone microarchitecture

Images from high-resolution peripheral quantitative computed tomography (HR-pQCT) (Xtreme CT, Scanco Medical, AG, Brüttisellen, Switzerland), of the non-dominant distal radius and distal tibia (the opposite limb in the presence of a previous fracture) will be obtained to measure bone geometry, cortical morphology, trabecular morphology, and overall biomechanical competence. In in-vitro studies estimated bone strength of the radius using finite element analysis [22, 23] which has been shown to be more closely correlated to observed radius bone strength than areal BMD by DXA [22]. PTH 1-34 treatment has been shown to be associated with an increase in vertebral estimated bone strength [24] and preservation of the estimated bone strength of the radius and hip [25, 26]. The images are obtained at baseline, 6, 12, 18, and 24 months (Table 2). The reported outcomes will be total BMD, cortical thickness, cortical porosity, bone volume per trabecular volume (BV/TV), trabecular number, trabecular thickness, and finite element failure load. The scanning protocol and the image acquisition have previously been described in detail [22, 23].

##### Serum bone turnover markers

Markers of bone formation (procollagen type-1 amino-terminal propeptide (P1NP)) and bone resorption (carboxy-terminal type-1 collagen crosslinks (CTX-1) will be measured by the method of chemiluminescence (iSYS, Immunodiagnostic Systems Ltd., Boldon, England). Sclerostin is analyzed using TECOmedical Human Sclerostin HS ELISA (TECOmedical group, Sissach, Switzerland). Bone turnover is affected by treatment with PTH 1-34, and studies have shown that a rise in the marker of bone formation, P1NP, during PTH 1-34 treatment is a predictor of the increase in BMD [27]. The assessment of bone biomarkers will allow exploration of mechanisms of action of WBV in augmenting PTH 1-34 treatment on bone turnover. The blood samples are taken at baseline, 3, 6, 12, 18, and 24 months (Table 2) after an overnight fast and stored at − 70 °C until analyzed in a central laboratory.

##### Functional biomarkers

Functional biomarkers including measurements of muscle strength, function and balance is measured by: (1) Timed Up and Go (TUG), (2) Short Physical Performance Battery (SPPB), (3) leg extensor power (Nottingham power rig), and (4) grip strength (Smedley dynamometer, TTM, Tokyo, Japan).

Fragility fractures are most often associated with falls [21, 28]. The measurement of lower extremity function and mobility will indicate if WBV has the potential to reduce the risk of falls in osteoporotic patients, which is another important determinant of the risk of fracture, independent on the effects on bone [21]. The TUG is the measurement of functional mobility and is a simple and reliable clinical test used to screen for fall risk in community-dwelling older persons [29]. Lower-extremity function and balance can also be assessed by the SPPB which is a validated test in older adults [30].

Leg extension power is assessed using a leg extensor power rig, (Medical Engineering Unit, School of Biomedical Sciences, University of Nottingham Medical School, Nottingham, UK) reported to have good reliability with no significant differences found between two tests performed 1 week apart (*r* = 0.97; coefficient of variation = 9%) [31]. At each visit the same leg is tested with a series of five measurements from the same starting position. The leg is selected randomly at the first visit. The SPPB and the TUG are described in detail by others [30, 32]. Reduced grip strength is a predictor of fragility fractures independent of BMD [33]. A reliable and valid method is by using a Smedley dynamometer (TTM, Tokyo, Japan). The measurements are done twice with each hand using a protocol described by others [34].

The functional tests will be performed by technicians, who all have been trained by a physiotherapist and all tests are conducted by standardized protocols. The TUG, SPPB, grip strength and leg extension power tests will be performed at baseline, 3, 6, 12, 18, and 24 months (Table 2).

Full-body DXA (Hologic Discovery, Waltham, MA, USA) is performed at baseline, 12, and 24 months to assess muscle mass (Fig. 2).

Sarcopenia is a condition with low skeletal muscle mass leading to decreased muscle strength, and impaired physical function, associated with an increased risk of falls [35]. Sarcopenia is proposed to be assessed by a variety of measurements of muscle mass and function including but not limited to full-body DXA, SPPB, grip strength, and gait speed [36, 37].

##### Questionnaires

The participants’ physical activity will be measured by a validated questionnaire, the International Physical Activity Questionnaire (IPAQ). The participants’ multiples of the resting metabolic rate will be generated (MET-min/week) [38].

Vertebral fractures have been shown to decrease quality of life [3] and the EuroQol 5-dimension, 5-level questionnaire (EQ-5D) is a well-validated measure of quality of life [39, 40].

The patients’ own fear of falling is associated with the risk of falls [41] and the the Falls Efficacy Scale International (FES-I) questionnaire, which is a reliable and validated questionnaire to measure the fear of falling in an older population [42].

The questionnaires IPAQ, EQ-5D, and FES-I will be distributed in paper versions to the participants at baseline, 12, and 24 months.

##### Adherence

Adherence to WBV is ascertained using self-reported adherence in a log book. Dropouts and the reasons for this will be noted. The adherence to the PTH 1-34 treatment is ascertained by asking the patients and by using the prescription database.

##### Side effects

Information on symptoms of dizziness, pain, and falls will be collected. The participants will be handed a calendar to note fall events, defining a fall as “an unexpected event in which the participants come to rest on the ground, floor, or lower level” [43]. Pain will be assessed by the Numeric Rank Score (0 being no pain, and 10 being unbearable pain) and the question about how many days they have felt dizzy during the last week, and falls will be assessed by monthly telephone calls during the first year and then every 3 months for the rest of the trial.

Demographic data, including data on risks factors associated with osteoporosis and fragility factures, will be collected at baseline and thus before randomization.

These factors include Body Mass Index, current and previous height, age, comorbidity, fall history, previous fractures, vitamin D and calcium intake, current, and previous history of medication.

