### Intervention

After instructions by nurses in the treating clinics all participants will self-administer subcutaneously (s.c) PTH 1-34 (20 μg s.c. daily) during the study. The participants follow each clinic’s control program including measurements of serum calcium and creatinine throughout the study. Medical records will be used to check the adherence to the PTH 1-34 treatment.

Half of the participants will be randomized to an intervention group, receiving WBW as add-on treatment. WBV will be undertaken using power plate My5 (Power plate®, UK). The power plate machine oscillates in all three planes, with a frequency of 30 Hz and amplitude of 1 mm (low displacement) and peak acceleration of 35.53 ms^-2^ rms (3.6 *g*).

The WBV intervention will be performed three times a week according to a training protocol (Table 1). The vibration platforms will be delivered and installed in the participant’s own home and instructions for use and the training program will be given by one of the investigators (DJ).

**Table 1 Tab1:** Training protocol

Week	First training day	Second training day	Third training day
1	30 s × 2	30 s × 3	30 s × 4
2	1 min × 1	1 min ×2	1 min × 3
3–5	1 min × 4	1 min × 4	1 min × 4
6–7	1 min × 5	1 min × 5	1 min × 5
8 to the end of study	1 min × 6	1 min × 6	1 min × 6

*Min* minutes, *s* seconds

The WBV intervention will be conducted with the knees slightly bent (at approximately 20°) to prevent vibrations to cause side effect as dizziness from the vibration transmitted to the head. The training period will be followed by a resting period in the ratio 1:1 and the training days will be conducted with a resting day in between.

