## Discussion

This is a RCT in osteoporotic patients randomized to PTH 1-34 treatment alone or to combined PTH 1-34 treatment and WBV. The primary and secondary endpoints in the study are chosen because previous studies have shown such markers of bone mass, microarchitecture, and turnover, as well as indices of physical performance, to be associated with osteoporosis or fragility fractures.

Earlier studies have reported WBV as a feasible intervention [12] and in older patients the adherence is reported to be good [19].

The intervention is designed to be of long duration (12–24 months) and the setting at the participants’ own home makes the training easy and highly accessible.

The study has limitations including the non-blinded design. It is our hypothesis that the primary endpoint, the BMD as well as a number of secondary endpoints (bone microarchitecture and bone turnover markers) are not at risk of bias by the open-label design. The functional biomarkers on the other hand could be affected by the non-blinded design but the study personnel performing the tests are blinded to the allocation and the baseline data is collected before randomization.

Measurements of quality of life, physical activity, and the FES-I questionnaire are patient-collected data, resulting in the possibility of bias in the reporting.

To limit the possibility of bias by attention, the participants will receive close to an equal amount of contacts by the investigators because of the “at home training design.”.

The study is partially blinded and is protected against selection bias by central randomization after baseline measurements, randomization via web with no stratification, and by allocation concealment.

It is our hypothesis that the DXA, HR-pQCT, and bone marker measurements are not at risk of performance bias. The physical biomarkers may be prone to performance bias, but the test personnel will be blinded to avoid evaluation bias.

To avoid attrition in both arms and ensure adherence, the participants are contacted by telephone each month during the first year and every third month during the second year. The participants receive a direct telephone number and mailing address to the primary investigator and are encouraged to make contact in case of any questions or events.

Every patient is motivated to attend follow-up regardless of randomization or adherence. The participants do not receive payment but are reimbursed for transport expenses.

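### The dizziness question looks back one week at calls one to three months apart, so it measures prevalence at the calls and cannot give cumulative incidence or reliably catch early, transient dizziness

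*Protocol article*

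**What the plan says.** All references are to the protocol article.

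- **Study objectives** lists the safety of WBV, with adherence, as an aim.
- **Intervention** explains the bent-knee stance as a measure "to prevent vibrations to cause side effect as dizziness from the vibration transmitted to the head".
- **Side effects** says that dizziness, pain and falls will be recorded, and describes the instrument in one loosely built sentence: "the question about how many days they have felt dizzy during the last week, and falls will be assessed by monthly telephone calls during the" opening 12 months, then every 3 months. **Discussion** repeats the schedule: "the participants are contacted by telephone each month during the first year and every third month during the second year".
- **Table 1** builds the vibration load from two 30-second bouts on the first training day to six 1-minute bouts. The last row, at full load, is labelled "8 to the end of study".
- Falls are handled differently: "The participants will be handed a calendar to note fall events". **Table 2** lists falls, and the WBV training log book, as continuous. Dizziness does not appear in Table 2.
- Other routes exist. **Adherence** provides for a self-reported WBV log book and for recording why participants drop out. **Discussion** adds that participants have a direct line to the investigator and "are encouraged to make contact in case of any questions or events".

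**The concern.** The recall window (7 days) is much shorter than the interval between calls (about one month, then three). Both are stated, so this is a mismatch in the text and not a detail left to a fuller document. Days outside the window are not asked about.

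The gap matters most at the start. The load changes over the first weeks, and a woman who feels dizzy then can cut back her sessions. If the dizziness has stopped by the first call, she truthfully answers zero days. The item then records nothing of the episode, although she stays in the trial.

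What is at stake is how far the stated safety objective can be met. The share of women who ever had dizziness on WBV, and when it began, cannot be obtained from this item.

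**Working it through.** The plan states no coverage figure, so there is none to reproduce. The check uses the plan's own schedule.

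**Inputs**
- Recall window: 7 days (Side effects: "the question about how many days they have felt dizzy during the last week").
- Calls: "monthly telephone calls during the first year and then every 3 months for the rest of the trial" (Side effects), taken as 12 in year 1 and 4 in year 2.
- Ramp-up: full load starts in week 8 (Table 1), so ramp-up is weeks 1–7, or 7 × 7 = 49 days.

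**Share of days covered** = (number of calls × 7) / 365

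| Period | Calls | Days covered | Share covered | Share not covered |
|---|---|---|---|---|
| Year 1 | 12 | 84 | 23.0% | 77.0% |
| Year 1, if 11 calls | 11 | 77 | 21.1% | 78.9% |
| Year 1, if 13 four-weekly calls | 13 | 91 | 24.9% | 75.1% |
| Year 2 | 4 | 28 | 7.7% | 92.3% |
| Year 2, if 3 calls | 3 | 21 | 5.8% | 94.2% |

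Over both years: (84 + 28) / 730 = 15.3% covered.

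**Ramp-up.** Count days from the start of WBV and space the calls 28 to 31 days apart.
- First window: days 22–28 (28-day spacing) to days 25–31 (31-day spacing). Weeks 3–5 are days 15–35 and have a constant load in Table 1, so the window falls wholly inside that plateau.
- Second window: days 50–56 to days 56–62, after full load has begun on day 50.
- Covered in weeks 1–7: 7 of 49 days = 14.3%; not covered: 42 of 49 = 85.7%.
- Covered in weeks 1–2: 0 of 14 days.

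**Sensitivity to the starting point.** The article does not say whether the calls are timed from randomization or from delivery of the platform. If WBV starts later than the call clock, the windows move earlier in the ramp-up. With 28-day spacing and a 7-day lag they become WBV days 15–21 and 43–49, which is 14 of 49 days (28.6%). No lag can give more than 14: at 28- to 31-day spacing, 49 days hold one full call cycle (7 covered days) plus a remainder of 18–21 days, which can hold at most one more window. Weeks 1–2 stay uncovered unless the lag is at least 8 days, since the first window then opens on day 22 − 8 = 14.

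**The case against.** The strongest reply is that a short-recall item, repeated up to 12 times in year 1 and asked in both arms, is a conventional and defensible instrument. Memory for dizziness over one to three months is poorer than over a week. This stands: the item gives a fair between-arm comparison of prevalence at the call times.

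Second, the question is not the only source. Missed sessions should show in the log book, reasons for dropping out are recorded, and participants may report events unprompted. A reader might infer that 77% of year 1 goes unobserved, or that women who stop early are counted as unaffected. The article supports neither. What can be said is that those days are not covered by the scheduled question. The other routes are incomplete, however: reasons are promised for dropouts and not for skipped or shortened sessions, and unsolicited contact is passive.

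Third, a reader might assume that intolerance is most likely during the ramp-up. Nothing in the article says so. If dizziness follows load, the full-load period from week 8 is the one that most calls sample. The ramp-up gap is a gap in coverage, not evidence that most dizziness is missed.

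Fourth, a reader might worry about a stop-versus-continue comparison of dizziness in year 2. None is planned: the Randomization section gives the purpose of re-randomization as seeing whether benefits last. Only women re-randomized to continue are still exposed, about 20 / 2 = 10 if the arm fills and splits evenly, so the year 2 gap matters less.

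Finally, call scripts may sit in a fuller protocol. That is possible, and the sentence is loosely worded. But the article does specify the dizziness item, and the recall period it gives does not match the interval.

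**Conclusion.** The point holds as a limit on safety capture. The scheduled dizziness question covers about 23% of year 1, about 8% of year 2 and 7 of the 49 ramp-up days, with weeks 1–2 not covered. It measures prevalence around each call, under whatever amount of vibration the women were then doing. It cannot give cumulative incidence, and it can miss early, transient dizziness in women who cut back WBV and remain in the trial.

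This assumes that the dizziness question belongs to the telephone calls, which is the natural reading, that calls run on schedule, and that their clock starts with WBV. A later WBV start could raise ramp-up coverage to 14 of 49 days at most.

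It would go too far to conclude that the trial will find WBV well tolerated because of this item. Only the WBV arm can cut back vibration, so any loss of early episodes through cutting back would fall on that arm. But the article gives no rate of dizziness or of cutting back from which to size it, and states no rule for calling WBV well tolerated. The primary endpoint, the sample size and the planned tests are unaffected. This is a cheap improvement.

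**What to change.** 1. Keep the last-week question as it is.
2. Add continuous or since-last-contact capture, the same in both arms. Preferably, have all participants mark dizzy days on the falls calendar they already hold. Otherwise add one identically worded question to the existing calls: *Since our last contact, have you felt dizzy, and on about how many days?*
3. Report the last-week item as prevalence at the call times and the new item as incidence.
4. Record dizziness as a reason for missed WBV sessions in the log book, and report it descriptively only. Do not count it as a between-arm event: controls have no WBV to miss, so in this open-label trial it would make ascertainment unequal.

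The cost is one mark on a calendar or one question on calls already planned, and slightly more burden for participants. If the question is used in place of the calendar, recall over one to three months will be poorer, which is a reason to prefer the calendar and to keep the 7-day item.

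Trial status gives September 2017 as the end of recruitment, before the article appeared in March 2018. If that was met, the early weeks have passed for all participants and cannot be recovered. For follow-up already collected, the remedy is to label the existing item as prevalence at call times and to report log-book gaps, dropout reasons and unsolicited reports beside it.
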